## 3.9. Data Quality Control

The baseline and end-line data will be collected by experienced and trained eight female midwives/nurses/ who are well familiar with the study's geographical area and can speak the local language (Afan Oromo. They will receive seven days of training on the data collection instruments, how to record the response of the mother, and anthropometric measurements. The training will be conducted just before the onset of the study followed by practical tests to make sure that skills were appropriately transferred. Also, a standardization exercise will be performed during the training to capture the technical errors in measurements. In each selected cluster, one trained supervisor will be assigned to give on-site support and oversee the completeness of collected data overnight. Also, the principal investigator will be made a weekly visit to check the completeness and quality of the collected data.

## 3.10. Pretest

All teams of the data collection will be involved in the pretest assessment. It will be conducted on 90 pregnant mothers two weeks before the real data collection in kersa district. This district is almost similar in socio-demographic and agroecological to the selected study area. This will enable us to check the reaction of respondents to the procedure and to test the data collection instrument for clarity, time consumption, and weather appropriately collect the intended information. Also, the appropriateness of statistical analysis ways will be tested. Finally, adjustments will be made based on the findings as necessary

## 3.11. Dietary intake assessment

To determine a minimum dietary diversity score, a single point will be awarded to each food group consumed over the reference period, and a total of all points calculated. The dietary diversity will be calculated by using the minimum DD-women (MDD-W) indicator, which is an improved version of the Women's Dietary Diversity (WDD) score and has 10 food groups, consumption of at least 5 of which indicates high dietary diversity. In addition, a multiple-pass 24 hrs recall method will be used to improve memory.

## 3.12. Anthropometric measurements

The pregnant mothers will be weighed at the begging and last ANC follow-up without shoes and with minimal or light clothing using a Seca digital scale. The readings will be taken to the nearest 0.1kg. It will be calibrated against known weight regularly. MUAC will be measured during the enrolment and at the end of the follow-up to assess wasting among the study subjects using an adult MUAC non-stretchable measuring tape to the nearest 0.1 cm. The Mid-upper arm circumference will be measured midway between the lateral projection of the acromion process of the scapula and the inferior margin of the olecranon process of the ulna.

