## 3.6. Study Variables

### 3.6.1. Dependent variables

- Birth weight
- Minimum dietary diversity scores
- Wasting (MUAC) and anemia
- Gestational Weight gain
- Nutritional Knowledge, attitude, and practice

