## 3.8. Data collection and instruments

The data will be collected in two phases. After the home-to-the-home census of eligible pregnant mothers enrolment, the baseline data will be collected by using pre-tested structured questioners, and guidance equations. Accordingly, data on socio-demographic characteristics, obstetrics history, MUAC, Hgb level, and 24-hour recall minimum women dietary diversity scores (FAO and FHI guideline 2016) will be collected. To get the best possible information, first, the mother will be asked to narrate what she remembers followed by probes to ascertain that no meal or snack will be left out. After all, a detailed list of all the ingredients of the dishes, snacks, or other foods consumed will be generated and grouped into ten. The end-line data will be collected after the mother gave birth, just within 24 hrs.

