## 3.13. Hemoglobin level Determination

Hemoglobin will be measured at baseline and end line using a portable, battery-operated photometer (HemoCue). After swiping the site with disinfectant, a finger prick will be made to obtain blood for hemoglobin measurement. The first two drops will be swapped away and the third drop will be used to fill the micro cuvette for reading the hemoglobin. The machine will be calibrated daily with a reference microcuvette provided with the machine. A trained and skilled laboratory technologist will be responsible for the collection of blood samples and hemoglobin determination.

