## 3.14. Statistical analysis

Data will be entered into Epi-data Version 3.1 for cleaning and sorting and then exported to SPSS version 20 for analysis. First, we will present descriptive information on the socio-demography of enrolled mothers, and then, baseline measurements will be compared between allocation groups by using mean difference or chi-squares. Comparison of the KAP scores, birth weight, hemoglobin level, and GWG, differences among the study arms will be done using ANOVA. The normality assumptions and the homogeneity of variance will be checked using a Q-Q plot and Levene’s test. The linear GEE regression analyses will be used to test the effects of the interventions on feto-maternal outcomes (birth weight and hemoglobin level) of difference in difference.

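### Nutrition KAP and gestational weight gain are compared between arms, but the listed enrolment baseline contains neither KAP nor body weight, and the weights appear to depend on ANC attendance

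*Protocol*

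**What the plan says.** Section 3.6.1 lists both "Nutritional Knowledge, attitude, and practice" and "Gestational Weight gain" among the dependent variables. Section 3.14 states: "Comparison of the KAP scores, birth weight, hemoglobin level, and GWG, differences among the study arms will be done using ANOVA". It gives no baseline term for either outcome; the difference-in-difference GEE model is named for birth weight and hemoglobin only.

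Section 3.8 itemises what is collected at baseline: "data on socio-demographic characteristics, obstetrics history, MUAC, Hgb level, and 24-hour recall minimum women dietary diversity scores". KAP and body weight are not in that list. The end-line round takes place within a day of delivery, and its content is not itemised. No section gives a time for a KAP measurement.

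Section 3.12 sets the two weights: "The pregnant mothers will be weighed at the begging and last ANC follow-up without shoes". The same paragraph treats arm circumference differently: "MUAC will be measured during the enrolment and at the end of the follow-up". Section 3.13 does likewise for hemoglobin: "Hemoglobin will be measured at baseline and end line".

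Women are found by a house-to-house census (Section 3.2.2) early in pregnancy (Section 3.7.1), not at an ANC clinic. Session 1 of the education is given at enrolment, and Sessions 2 and 3 at second- and third-trimester ANC appointments (Section 3.7.2). Table 2 adds monthly home visits by counselors.

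**The concern.** GWG is a last weight minus a first weight. If both are taken at ANC visits, the period over which gain is measured depends on when each woman first attends and when she last attends. Enrolment and first ANC attendance are separate events here, so the first weight can fall after the intervention has begun. The intervention arms have health-staff contact from enrolment and receive two of three sessions at ANC. If that contact leads women to attend earlier, or to keep attending later, their weighing interval is longer and their measured gain larger, whatever the intervention does to true gain. A woman with no ANC visit would have no GWG at all, and that missingness could also differ by arm.

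For KAP the issue is milder. It is the outcome the education targets most directly, yet no pre-intervention score is listed. If a baseline score is not taken before Session 1, no later analysis plan can recover it.

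**Working it through.** The protocol gives no figure for weekly weight gain, for ANC booking times or for the stability of KAP scores, so there is no stated figure to reproduce. The core of the check is a comparison of sections; the arithmetic only shows scale.

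**Sections side by side**

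| Outcome tested between arms (3.6.1, 3.14) | In the 3.8 baseline list? | Timing given elsewhere |
| --- | --- | --- |
| Hemoglobin | Yes | Baseline and end line (3.13) |
| KAP | No | None |
| GWG (body weight) | No | Beginning and last ANC follow-up (3.12) |

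Arm circumference, a further dependent variable, is in the list and is timed to enrolment and the end of follow-up in 3.12. Weight is therefore the only physical measure taken on the mothers whose timing is expressed through ANC. The end-line round cannot supply the closing weight, because it takes place after delivery.

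**GWG: shift from unequal weighing intervals**

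Shift = (difference between arms in length of weighing interval, weeks) × (gain per week). Assumed inputs: 1 to 6 weeks; 0.2 to 0.45 kg per week.

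- No gap: 0 kg.
- 1 week × 0.2 kg = 0.2 kg.
- 2 weeks × 0.3 kg = 0.6 kg.
- 4 weeks × 0.3 kg = 1.2 kg.
- 6 weeks × 0.45 kg = 2.7 kg.

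**KAP: chance imbalance**

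Inputs from Section 3.4: 116 women per arm, design effect 2 (assumed here to apply to KAP). Sections 3.4 and 3.5 give 18 clusters over three arms, 6 per arm.

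- Variance of a chance difference between two arm means, in SD² units: 2 × 2 / 116 = 0.0345.
- Standard deviation of that difference: √0.0345 = 0.19 SD.
- 95% range: ±1.96 × 0.186 = about ±0.36 SD.

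This variation is already carried in the standard error of an analysis that respects clustering. It is not a bias, but without a baseline it cannot be inspected or reduced.

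**KAP: precision forgone**

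Adjusting for a baseline score correlated r with the end-line score multiplies the residual variance by 1 − r², a reduction of r². With r assumed:

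- r = 0.4: 0.4² = 16%.
- r = 0.5: 0.5² = 25%.
- r = 0.6: 0.6² = 36%.

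**The case against.** Five points can be made against this.

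1. **The weight sentence is ambiguous.** Section 3.7.2 uses the same misspelt word for the start of the intervention at enrolment. Section 3.12 could therefore mean a weight at enrolment and another at the last ANC visit, and the bias at the starting end would disappear. This stands as a possibility. The contrast with the arm-circumference sentence in the same paragraph makes the ANC reading the more natural one. On either reading weight is missing from the 3.8 list, and the closing weight still depends on ANC.

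2. **The 3.8 list may not be exhaustive.** It gives no end-line content, so even birth weight, the primary outcome, is not itemised there. Section 3.14 speaks of comparing baseline measurements without naming them. A reader might infer that KAP definitely has no baseline. The text supports only that none is listed and that its timing is unstated.

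3. **An effect on ANC timing is not in the document.** No session topic concerns early booking, Sessions 2 and 3 use ordinary appointments, and all arms receive routine education from ANC providers. A reader might infer that the intervention will bring women to ANC earlier and so inflate GWG. That remains conjecture: the design makes it plausible and shows no more.

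4. **An end-line-only KAP comparison between randomised arms is valid.** This is right. It would be wrong to call the KAP comparison biased or uninterpretable; the loss is in checking balance and in precision.

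5. **Neither outcome is primary, and covariate adjustment is often left to an SAP.** True of the adjustment, but not of the data collection: an SAP cannot adjust for a score or a starting weight that was not obtained.

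**Conclusion.** The point holds as a modest and inexpensive improvement. Two outcomes tested between arms lack a clearly specified pre-intervention measurement, and Sections 3.8, 3.12 and 3.14 need to be reconciled.

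For GWG, on the natural reading of 3.12, both weights depend on ANC attendance. A difference between arms in the weighing interval would bias GWG by about 0.2 to 2.7 kg under the assumed gaps and weekly gains, and by nothing if there is no gap. The direction would favour the intervention if its women attended earlier or later than controls.

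For KAP, the comparison is valid, but imbalance of the order of ±0.36 SD between arms could arise by chance and go unseen. A variance reduction of 16 to 36%, at an assumed correlation of 0.4 to 0.6, would be given up. The primary outcome, birth weight, is not affected.

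**What to change.** - **Section 3.8:** add body weight, on the same scale, and the KAP questionnaire to the enrolment baseline in all three arms, completed before Session 1. List KAP in the end-line round as well. The protocol mentions structured questionnaires in general, so the KAP instrument should be named.
- **Section 3.12:** start GWG from the enrolment weight and record gestational age at both weights. Moving the first weight alone is not enough, because the last ANC weight depends on attendance just as much.
- **Section 3.14:** analyse gain per week between the dated weights, or adjust for the interval between them, so that the timing of the last ANC weight does not drive the comparison. If the weekly rate is thought to vary over pregnancy, adjusting for gestational age at each weight is the safer choice. Adjust the KAP comparison for its baseline score.

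The cost is a slightly longer baseline visit and carrying the scale on the home round. That visit already includes arm circumference, hemoglobin and a dietary recall.

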## 3.13. Hemoglobin level Determination

Hemoglobin will be measured at baseline and end line using a portable, battery-operated photometer (HemoCue). After swiping the site with disinfectant, a finger prick will be made to obtain blood for hemoglobin measurement. The first two drops will be swapped away and the third drop will be used to fill the micro cuvette for reading the hemoglobin. The machine will be calibrated daily with a reference microcuvette provided with the machine. A trained and skilled laboratory technologist will be responsible for the collection of blood samples and hemoglobin determination.

## 3.14. Statistical analysis

Data will be entered into Epi-data Version 3.1 for cleaning and sorting and then exported to SPSS version 20 for analysis. First, we will present descriptive information on the socio-demography of enrolled mothers, and then, baseline measurements will be compared between allocation groups by using mean difference or chi-squares. Comparison of the KAP scores, birth weight, hemoglobin level, and GWG, differences among the study arms will be done using ANOVA. The normality assumptions and the homogeneity of variance will be checked using a Q-Q plot and Levene’s test. The linear GEE regression analyses will be used to test the effects of the interventions on feto-maternal outcomes (birth weight and hemoglobin level) of difference in difference.

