# CHAPTER ONE: INTRODUCTION

## BACKGROUND OF THE PROBLEM

Adequate maternal nutrition before and during pregnancy will play a pivotal role in the health outcomes of the mother and neonate. (De Silva Lopes K et al., 2017, Ramalho AA et al., 2017, Christian. 2018,). Accordingly, the nutritional status of the mother at conception influences how nutrients will be portioned between the mother and fetus (Janet C et al., 2003). Thus, poor maternal nutritional status indicators during pregnancy like MUAC less than 21 cm and anemia were important predictors of adverse neonatal outcomes (Hutagalung, 2017, Joshua et al., 2018).

For insistence, low birth weights, stillbirths, and preterm births were among the most common ones related to inadequate nutritional status of the mother (Ota et al., 2015, Hutagalung, et al 2017).

Maternal undernutrition during pregnancy also contributes to fetal growth restriction, which increases the risk of neonatal deaths and, for survivors, of stunting by 2 years of age (Black et al., 2013, Solomons et al., 2015). Similar studies also reported that early onset of growth delay and prematurity significantly increases the risk for a neurological abnormality, motor, and cognitive delay *(Stefania Longo et al., 2013).* Evidence from famine studies revealed that maternal nutritional deprivation during mid and late pregnancy was associated with significantly reduced fetal birth weight. While, if it is during early pregnancy, there will be a decline in the cognitive ability of the fetus in later life (Schulz et al., 2010, de Rooji S et al., 2010). Other similar studies also show that inadequate maternal nutrition during pregnancy will determine (“programmed”) the later age bone mineral metabolism and development of heart failure ( Barker D J. Pet al., 2010, George M et al., 2014).

Food insecurity during pregnancy was not associated only with adverse child outcomes but, also has an association with many maternal complications like maternal anemia, depression/anxiety disorders in pregnancy, gestational complications (diabetes, hypertension, obesity, and dyslipidemia), low gestational weight gain which are again the determinant factors for poor fetal-outcomes (Stefania Longo et al., 2013, Schoenaker et al., 2014, (Ramalho AA et al., 2017,).

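### The birth-weight analysis in 3.14 names no baseline covariates, although maternal predictors called important are measured at entry; a short fixed list in the GEE would gain modest precision and correct chance imbalance

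*Protocol*

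**What the plan says.** Section 3.4 makes birth weight the primary outcome, with an expected gain of 100 g. Section 3.14 contains three statements that bear on how baseline data are used:

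- A comparison of arms at entry: "baseline measurements will be compared between allocation groups by using mean difference or chi-squares".
- An ANOVA: "Comparison of the KAP scores, birth weight, hemoglobin level, and GWG, differences among the study arms will be done using ANOVA".
- A regression: "The linear GEE regression analyses will be used to test the effects of the interventions on feto-maternal outcomes (birth weight and hemoglobin level"). The sentence goes on to describe this as difference in difference. It names no covariates.

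Elsewhere the protocol treats maternal nutrition at entry as prognostic and collects it. The Background states that "MUAC less than 21 cm and anemia were important predictors of adverse neonatal outcomes". Section 3.8 lists the baseline data as "data on socio-demographic characteristics, obstetrics history, MUAC, Hgb level, and 24-hour recall minimum women dietary diversity scores". Sections 3.12 and 3.13 confirm the timing: "MUAC will be measured during the enrolment and at the end of the follow-up to assess wasting" and "Hemoglobin will be measured at baseline and end line".

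Section 3.6.2 lists independent variables, among them maternal age and parity, but ties them to no model. MUAC and anemia appear in 3.6.1 as outcomes only.

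**The concern.** The protocol holds measured predictors of its primary outcome, but nothing in it brings them into the analysis of that outcome. ANOVA across arms cannot use them. The GEE could, but no covariate is named. Difference in difference does not fill the gap: a newborn has no earlier birth weight, so for this outcome the model reduces to a comparison of arms after delivery.

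A comparison of arms at entry shows an imbalance but does not correct it. With six kebeles per arm, appreciable chance differences in maternal nutrition or parity are likely in any one trial, and they carry into the birth-weight contrast. Covariates fixed in advance remove the part they explain and narrow the interval, using data that will be in hand anyway.

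**Working it through.** The plan gives no figure for the effect of adjustment, so there is none to reproduce. The sample size of 348 enters only through the number of women per arm; whether it follows from its stated inputs is a separate matter.

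**Inputs from the protocol.** 116 women per arm, design effect 2, 15% non-response, effect size 0.25 and target 100 g (3.4); six kebeles in each of three arms (3.5).

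**Assumptions.** The SD of birth weight is 400-500 g; 400 g is 100/0.25 if the effect size is read as a standardised difference. R² of birth weight on the baseline list is 0.02-0.12. The same R² and the same design effect are taken to hold within and between kebeles. The protocol supports none of these directly.

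**Step 1, unadjusted standard error of a two-arm contrast.** SE = SD × √(2 × 2/116) = SD × 0.186. This is 74.3 g at SD 400 g and 92.8 g at SD 500 g. After 15% loss, the effective number per arm is 116 × 0.85/2 = 49.3 and the factor is √(2/49.3) = 0.201, giving 80.6 g and 100.7 g. The ratios in step 2 do not depend on this choice.

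**Step 2, effect of adjustment.** Adjusted SE = SE × √(1 − R²). The part of the contrast due to a one-standard-error chance imbalance is √R² × SE.

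| Assumed R² | SE multiplied by | SE at SD 400 g / 500 g | Imbalance part at SD 400 g / 500 g |
|---|---|---|---|
| 0.02 | 0.990 | 73.5 / 91.9 g | 10.5 / 13.1 g |
| 0.05 | 0.975 | 72.4 / 90.5 g | 16.6 / 20.8 g |
| 0.10 | 0.949 | 70.5 / 88.1 g | 23.5 / 29.4 g |
| 0.12 | 0.938 | 69.7 / 87.1 g | 25.7 / 32.2 g |

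So the standard error falls by about 1% to 6%.

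**Step 3, what the imbalance part is.** It lies inside the unadjusted standard error. At R² 0.12 and SD 400 g, √(69.7² + 25.7²) = 74.3 g, which is the unadjusted figure. Adjustment removes this component of the sampling error; it does not remove a bias.

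**Step 4, power.** After loss and design effect, three-arm ANOVA power at an effect size f of 0.25 moves from 77.3% to 78.2%, 79.5% and 81.8% for R² of 0.02, 0.05 and 0.10. Two-sided pairwise power for 100 g at SD 400 g moves from 23.6% to 24.0%, 24.6% and 25.7%. The gain is real but small.

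**The case against.** The strongest reply is that a covariate list is commonly left to a statistical analysis plan, which may exist and is not shown. The GEE is a regression, the text does not call it unadjusted, and 3.6.2 lists maternal age and parity as independent variables. This stands in part: for the GEE, covariates are unstated, not excluded. But 3.14 does fix a covariate-free ANOVA for the primary outcome. Nor does 3.6.2 settle the matter: it omits MUAC and hemoglobin, and it includes pregnancy complications, which can arise after randomisation.

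Blocking is a second reply. Section 3.5 randomises kebeles within two agro-ecological blocks, which limits imbalance between areas. That also stands, but it does not balance maternal nutrition or parity among kebeles within a block.

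Three stronger readings are tempting, and the protocol does not support them:

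- A reader might infer that baseline values serve only to compare arms at entry. Baseline hemoglobin enters the difference-in-difference analysis of hemoglobin, and gestational weight gain uses the first weight. The gap is confined to birth weight.
- A reader might infer that covariates will be chosen from the baseline comparison. Section 3.14 does not say so, and a mean difference can be purely descriptive.
- A reader might set the 10-32 g imbalance part against the 100 g target as a distortion of the result. It is sampling error that the unadjusted interval already covers.

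**Conclusion.** The point holds as one of efficiency and of imbalance in the trial as realised, not of validity. Under randomisation the unadjusted comparison is unbiased on average. Section 3.14 fixes one birth-weight analysis that cannot use the baseline predictors and another that does not say whether it will.

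The gain from adjustment is about 1-6% in the standard error for an assumed R² of 0.02-0.12, together with correction of whatever chance imbalance in those predictors occurs among six kebeles per arm. The range depends on an R² that the protocol does not give. The percentage does not depend on the SD, but the gram figures do. If the predictors explain less of the variation between kebeles than within them, the gain is smaller. It is a worthwhile improvement because it costs almost nothing; it would not by itself change whether the trial can detect 100 g.

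**What to change.** In 3.14, make the primary birth-weight analysis the linear GEE clustered on kebele, with terms for:

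- study arm;
- agro-ecological block (district), since randomisation was done within it;
- baseline MUAC and baseline hemoglobin, both continuous, so that a cut-off does not discard information;
- parity and maternal age.

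Use entry values only, because end-line MUAC and hemoglobin can be affected by the intervention. State that this model applies whatever the baseline table shows. Report the unadjusted comparison, also clustered on kebele, as a sensitivity analysis. Drop the difference-in-difference label for birth weight and keep it for hemoglobin.

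Replacing the GEE with an ordinary regression on arm and covariates would not do, because it would lose the clustering and could omit the block.

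The cost is one paragraph in 3.14. All the variables fall within the baseline data already planned, so no extra measurements or women are needed.

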# Abstract

**Background**: Adequate maternal nutrition before and during pregnancy plays a key role in the health outcomes of the mother and neonate. Nutrition-sensitive programs are important in the prevention of maternal malnutrition, especially in low-income countries like Ethiopia. Home gardens are a part of the nutrition-sensitive agricultural programs practiced in many developing countries. In addition to this, home gardens are a time-tested local strategy that is widely adopted and practiced in various circumstances by local communities with limited resources and institutional support. However, there were inconsistent reports on the improvement of nutritional status and feto-maternal outcomes of pregnancy. In addition to this, to our knowledge, there is no report from the study area on the synergistic effect of home gardening and nutritional education on pregnancy outcomes.

**Objective:** the objective of this study is to assess the combined effect of nutritional education and home gardening interventions on feto-maternal outcomes among pregnant women of Jimma zone, southwest Ethiopia.

**Methodology**: The study design will be a cluster randomized controlled trial done on pregnant mothers from August 2020 to December 2019. Two districts will be selected randomly one from each agro-ecological area of the zone (predominantly coffee growing and grain growing). Then, non-adjoining Kebeles/clusters will be identified and marked on the map. Finally, by using a random sampling method clusters from both districts will be assigned to the intervention or control group. The sample size will be determined by G-power 3.1. The number of pregnant mothers to be involved in the study from both woreda will be made by the population proportion of each cluster. The statistical analysis method to be used will be descriptive, Oneway analysis of Variance, and the Generalized estimating equation model will be used.

**Resul**t: The result of this study will be described and displayed in tables and figures. The total budget needed for the study will be 603,130 ETB. The conclusions and recommendations will be drowning based on the result.

Keywords: Pregnancy, Home gardening, Pregnancy outcomes, Nutritional education.

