### 3.2.2. Study Units

The selected study clusters will be the study unit. First-trimester pregnant mothers who will participate in the study will be a unit of analysis. Mothers who will participate in the study will be identified by doing home to a home census of the study clusters and fulfilling the criteria.

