## 3.4. Sample Size Determinations

The sample size was estimated by G power version 3.1.9.7. Assumptions used to calculate the required sample size were: precision of 5%, power of 80%, an effect size of 0.25, and we expect a mean birth weight change of 100 gm (the primary outcome) in the intervention groups (from 2975 g to 3075 g) based on previous studies. Design effects of 2 and 15% non-response rates were also considered. The total sample size was 348 pregnant women (116 per each of the three study arms).

The sample size for each study cluster (kebele) will be allocated based on the proportion of their respective population. Accordingly, a total of eighteen clusters (kebeles) will be selected. From Mana and Seka districts eight and ten clusters (kebeles) respectively.

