## 3.5. Sampling procedures

Two districts (woreda) that could represent the two known agroecological areas of the Jimma zone will be selected. Accordingly, Mana from predominantly coffee-growing districts and Seka Chekorsa from grain and crop-growing districts were selected purposively for management and logistical reasons. Then, non-adjacent clusters or kebeles (the smallest administrative units) will be selected from both districts to have buffer zones**.** Accordingly, a total of 18 clusters (8 from Mana and 10 from Seka chekorsa) districts will be selected. Using the randomized complete block design; the clusters (kebeles) will be grouped into two blocks based on their agroecological areas (mainly coffee or grain producing). Finally, from both blocks clusters will be randomly assigned to the three study arms (husband, Peers, and control). Thus, Nase, Bidaru toli, Dimtu (of Seka), Doyo toil, Gudata bula, and Lemi Lelisa clusters(kebeles) will be assigned to the husband group. While, Siba bake, Buyo kechema, Meti, Bore, Bebela kosa, and Haro clusters will be assigned to the peer group. Likewise, Komo hare, Gepa seden, Wakito madalu, Kamise waraba, kore Lelisa, and kenteri clusters will be assigned to the control group.

Regarding the sample size allocation, it was proportionally to the population size of respective districts and kebeles (clusters). A total of 348 first-trimester pregnant women will be enrolled at baseline, 144 women will be from the mana district (48 women in each arm), and 204 women will be from the Seka-chekorsa district (68 women in each arm). This means that a total of 116 1^st^ trimester pregnant women per the three study arms will be enrolled. All of the first-trimester pregnant women who will fulfill the inclusion criteria in each cluster will be enrolled until the desired or allocated number will be achieved.

[figure not shown]

Figure 2. Map of the study area with selected study clusters (kebeles) of both districts (Seka and Mana) source: Generated using ArcGIS software version 10.3 from ETHIO-GIS, 2014 database.

Jimma zone

21 Districts ( woredas)

Goma,

Limu kosa

Mana

Gera

Gumay

Limu seka

Boter –tolay

Chora- boter

Shebe- sombo

Non benja

Omo- Nada, Omo-Beyam

Sekachekorsa

Mancho

Dedo

Kersa

Tiroafata

Sokoru,

Santama

Sigimo

Gatira

Predominantly Grain/crops producing districts.

11 districts

---

Predominantly coffee growing districts,

10 districts

Mana district selected

Mana district

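### One-way ANOVA on individual women compares the arms although kebeles are randomised and a design effect of 2 is assumed; for KAP and GWG it is the only named test

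*Protocol*

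**What the plan says.** Allocation is by kebele. Section 3.5 says that "from both blocks clusters will be randomly assigned to the three study arms (husband, Peers, and control", and section 3.4 that "a total of eighteen clusters (kebeles) will be selected". The sample size allows for this: "Design effects of 2 and 15% non-response rates were also considered", giving "The total sample size was 348 pregnant women (116 per each of the three study arms".

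For the analysis, section 3.14 says: "Comparison of the KAP scores, birth weight, hemoglobin level, and GWG, differences among the study arms will be done using ANOVA". The Abstract lists the methods as "descriptive, Oneway analysis of Variance, and the Generalized estimating equation model will be used". The stated assumption checks are a Q-Q plot for normality and Levene's test for equal variances.

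Section 3.14 then names a linear GEE to test the intervention effects on birth weight and hemoglobin, described as a difference in difference. It does not name the kebele, or any other unit, as the GEE's cluster. It does not rank the GEE against the ANOVA.

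**The concern.** One-way ANOVA treats the women as independent. Randomising kebeles breaks that assumption, and neither stated check (Q-Q plot, Levene) examines it. A design effect of 2 means that the authors expect the variance of an arm mean to be twice what ANOVA will estimate. The sample size and the test therefore rest on incompatible assumptions.

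If the women in a kebele resemble one another as section 3.4 supposes, the ANOVA p-values are too small and the matching intervals too narrow. For KAP and GWG, both dependent variables in section 3.6.1, there is no other named test to fall back on. For birth weight and hemoglobin, two tests with different error rates would both be available, with no rule on which one counts.

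**Working it through.** **Inputs**
- From section 3.4: "precision of 5%, power of 80%, an effect size of 0.25". I read the 5% as alpha and the effect size as Cohen's f for a three-arm ANOVA; the protocol confirms neither.
- Design effect (DE) 2, 15% non-response, 348 women and 18 kebeles (section 3.4).
- Three arms of 6 kebeles (section 3.5). Section 3.3 speaks of two arms; I follow 3.4, 3.5 and Figure 3.
- The ICC is not given, so it is derived below and then varied.

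**The plan's own figure.** With f = 0.25, alpha 0.05, power 0.80 and three groups, the noncentral F gives 158 women (159 balanced). Times 2 this is 316–318. With 15% non-response it becomes 363–366 (×1.15) or 372–374 (÷0.85), against 348 stated. The 348 fits a 10% allowance: 158 × 2 × 1.1 = 347.6. So the figure does not reproduce as described. That is a separate matter and does not affect the error rates below, which depend on DE.

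**Implied ICC.** Mean cluster size m = 348/18 = 19.33. From DE = 1 + (m − 1) × ICC, ICC = (2 − 1)/18.33 = 0.0545.

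**Type I error of the unadjusted test (large-sample)**
- Omnibus, 2 df: P(χ²₂ > 5.99/DE). At DE = 2: P(χ²₂ > 2.996) = exp(−1.498) = 22.4%.
- One pairwise contrast: 2 × [1 − Φ(1.96/√DE)]. At DE = 2: 2 × [1 − Φ(1.386)] = 16.6%.

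**After 15% loss at the same ICC.** Women: 348 × 0.85 ≈ 296. m = 16.4 and DE = 1 + 15.4 × 0.0545 = 1.84. Omnibus: exp(−2.996/1.84) = 19.7%. Pairwise: 14.9%.

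**Simulation check.** 40,000 null trials per layout, ordinary F test on women, ICC 0.0545:

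| Layout | Omnibus | Pairwise |
|---|---|---|
| 348 women, near-equal kebeles | 22.1% | 16.4% |
| Unequal kebeles from the 48/68 district split per arm | 22.9–23.2% | 16.9–17.0% |
| About 15% of women lost | 19.6% | 15.0% |

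**Sensitivity to the ICC** (simulated, 348 women, near-equal kebeles):

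| ICC | DE | Omnibus | Pairwise |
|---|---|---|---|
| 0 | 1.00 | 5.2% | 5.2% |
| 0.01 | 1.18 | 7.9% | 7.4% |
| 0.02 | 1.37 | 11.2% | 9.5% |
| 0.03 | 1.55 | 14.6% | 11.8% |
| 0.05 | 1.92 | 21.0% | 15.8% |
| 0.10 | 2.83 | 35.0% | 24.4% |

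An ANOVA on the 18 kebele means, F(2,15), holds 5%. This is exact for equal cluster sizes and normal data.

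**The case against.** The best defence is that section 3.14 has two steps: ANOVA describes the arms, and the GEE tests the intervention effect. Birth weight is the primary outcome, and GEE is a method for correlated data. On that reading the trial's main test need not be the faulty one. This stands in part. A reader might infer that the trial's primary test has a 20% false-positive rate; the protocol does not support that, because a GEE clustered on kebele could be what decides. What remains is that the protocol does not say so, and that ANOVA is still listed as an arm comparison for birth weight.

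A reader might also infer that the GEE is itself invalid, either through clustering on the woman or through an uncorrected variance with 18 clusters. The protocol fixes neither. The subject variable, working correlation and small-sample correction are commonly left to an SAP, so their absence is no defect here.

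Two further points stand. The protocol states no ICC, and a rounded planning design effect may be conservative, so a single unconditional error rate would claim too much. And the statement in section 3.2.2 that "First-trimester pregnant mothers who will participate in the study will be a unit of analysis" is not evidence of the error, since a mixed model or a GEE also analyses women.

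Finally, KAP and GWG are not named in the hypotheses or specific objectives, though GWG may fall under nutritional status. That lowers the stakes for the two outcomes that have no other test. It does not make the test valid.

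**Conclusion.** The protocol names a test that contradicts its own design and sample size. This is not detail deferred to an SAP, because the test is stated. The point is firmest for KAP and GWG, where ANOVA is the only named test. For birth weight and hemoglobin the defect is an unadjusted ANOVA beside a GEE, with no statement of which decides.

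The size is conditional on the planning design effect of 2, applied alike to all four outcomes: about 20–22% for the omnibus test and 15–17% for one pairwise contrast, against a nominal 5%. At ICC 0.01 to 0.02 the omnibus rate is about 8–11%, which is smaller but still above 5%. If the authors expect an ICC that low, then the design effect of 2 needs another justification.

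**What to change.** In section 3.14 and the Abstract, limit one-way ANOVA on women to description, without p-values for arm differences. Name one analysis that accounts for kebele for KAP, birth weight, hemoglobin and GWG. Any of these would do:
- GEE clustered on kebele, with a small-sample-corrected variance and a t reference;
- a linear mixed model with a random kebele intercept and small-sample degrees of freedom;
- a comparison of the 18 kebele means, which any package can run.

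State that this is the single primary analysis of birth weight. The small-sample correction is worth naming. In 6,000 simulated null trials on this layout, a kebele-clustered GEE with uncorrected sandwich errors rejected in 10% (pairwise) and 14% (2-df Wald), against 4% with the Mancl-DeRouen correction and t(15).

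Cost: no new data or visits. At design effect 2, intervals widen by √2 = 1.41 relative to the unadjusted ones. With a t(15) reference the factor is 1.41 × 2.131/1.967 = 1.53. Power also falls once only 18 clusters are counted. With f = 0.25 the noncentrality is 348 × 0.0625/2 = 10.9, and F(2,15) gives about 76% power, or about 73% after 15% loss, against the planned 80%. The sample-size section should acknowledge this.
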